#### Cost-effectiveness analysis

In subsequent analyses, a trial-based economic evaluation will be conducted based on the help-seeking intention scores, the intervention costs, and mental health-related services costs. Intervention costs include the intervention development costs (e.g. planning, development, and production stages of video). Mental health services cost will be calculated by applying standard Australian unit costs (i.e. Independent Hospital Pricing Authority [17], Medicare Benefit Scheme fees [18]) to the resource use units collected through the HSUQ. Mean values of costs and help-seeking intention scores will be reported for both groups and assessed by generalised linear models. An incremental cost-effectiveness ratio (ICER) will be calculated as the difference in average cost between the groups, divided by the difference in help-seeking intention scores. Nonparametric bootstrapping will be used to obtain confidence intervals for incremental cost-effectiveness ratios. A modelled economic evaluation will also be undertaken using the results of this trial and relevant epidemiological literature to extrapolate long-term costs and consequences associated with help-seeking intentions.

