## Methods

### Study design

This is a single-blinded, two-arm RCT comparing the effects of an intervention video against a control video. We plan to recruit 446 adult Australian men to be randomised, with a 1:1 allocation (223 participants per arm).

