### Sample size and power analysis

The sample size is calculated to detect a 0.25 standardised difference in mean on the GHSQ-Self score between the intervention and control group (90% power, 2-sided 5% significance level), assuming a correlation of 0.67 between T1 and T2 scores. This sample size of 446 participants also allows for 20% loss to follow-up. We have chosen a relatively small effect size given the universal nature of the intervention, where we would aim to create change by producing a small effect on a large number of men, and given that we are measuring intentions to seek help as the primary outcome, rather than actual help-seeking behaviour. Intentions was chosen over behaviour as the primary outcome given the small amount of time between T1 and T2 in which participants would have the opportunity to seek help as the need arose.

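### The trial-based ICER, read plainly, spreads the one-off cost of making the video over the men enrolled and not over the audience it is made for

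*Protocol article*

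**What the plan says.** The Cost-effectiveness analysis section of the protocol article settles three things.

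- The evaluation belongs to the trial: "a trial-based economic evaluation will be conducted based on the help-seeking intention scores, the intervention costs, and mental health-related services costs".
- The cost of making the video is counted: "Intervention costs include the intervention development costs (e.g. planning, development, and production stages of video".
- The ICER is "calculated as the difference in average cost between the groups, divided by the difference in help-seeking intention scores".

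A second, modelled evaluation is planned, "using the results of this trial and relevant epidemiological literature to extrapolate long-term costs and consequences associated with help-seeking intentions". The description does not mention the number of viewers or how the production cost is to be spread.

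The groups are defined under Study design: "We plan to recruit 446 adult Australian men to be randomised, with a 1:1 allocation (223 participants per arm". The intended use is much wider. The Sample size section calls the intervention universal and says "we would aim to create change by producing a small effect on a large number of men". The Background and Dissemination sections describe public release with a supporting media campaign if no net harm is found.

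**The concern.** Making a video is a fixed cost: it is the same whether 200 or 200,000 men watch it. An average cost per man in a trial arm divides that amount by the arm size, which was chosen for power on the help-seeking score and has nothing to do with reach. The intervention video was made specifically for this study, and the control is a section of a longer documentary, so the cost of making the intervention video falls into the difference between arms.

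A ratio built this way answers what it would cost per point if only the trial participants ever saw the video. That is not the use the article describes. The Background also gives the production cost and viewing time of the 3-hour documentary as the reason to test a short video, so readers will look to the ICER for an answer about cost per effect.

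**Working it through.** **The plan's own figure.** The article states no cost and no ICER. The figure that matters is the arm size. Inputs from the Sample size section: "0.25 standardised difference in mean on the GHSQ-Self score between the intervention and control group (90% power, 2-sided 5% significance level", correlation 0.67 between T1 and T2, 20% loss. With the baseline-adjusted variance factor 1 − 0.67² = 0.5511, n = 2 × 0.5511 × (1.960 + 1.282)² / 0.25² = 185.3 per arm. Multiplied by 1.2 this is 222.4, so 223 per arm and 446 in total, as stated.

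**The ICER as defined.** Let D be the one-off development cost, n the arm size, S the difference in other cost per man and E the difference in help-seeking score. Then

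ICER = (D/n + S)/E = D/(n × E) + S/E.

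Only the first term depends on n, and it falls as 1/n. The second does not scale this way.

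**Illustration.** None of these inputs is in the article; all are assumptions. D = AUD 100,000, 300,000 or 1,000,000; score SD = 10, so E = 0.25 × 10 = 2.5 points; S = 0.

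| Divisor | D per man (AUD) | ICER (AUD per point) |
|---|---|---|
| 178 (223 less 20% loss) | 562 / 1,685 / 5,618 | 225 / 674 / 2,247 |
| 223 (planned arm) | 448 / 1,345 / 4,484 | 179 / 538 / 1,794 |
| 446 (trial doubled) | 224 / 673 / 2,242 | 90 / 269 / 897 |
| 10,000 viewers | 10 / 30 / 100 | 4 / 12 / 40 |
| 100,000 viewers | 1 / 3 / 10 | 0.40 / 1.20 / 4.00 |

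For an SD of 8 to 12 (E = 2 to 3) and the same range of D, the ICER at 223 per arm runs from AUD 149 to 2,242 per point.

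**What does not depend on D or E.** The ratio of the development term at 223 men to the same term at an audience A is A/223. That is 10,000/223 = 44.8 and 100,000/223 = 448. Doubling the arm halves the term.

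**Can it change the reading?** Take D = AUD 300,000, E = 2.5 and an assumed service saving of AUD 50 per man (S = −50). At 223 men the ICER is (1,345 − 50)/2.5 = +518. At 100,000 viewers it is (3 − 50)/2.5 = −18.8. Under these assumptions the divisor alone decides whether the video adds cost or saves it.

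**The case against.** The strongest objection is that the divisor is inferred. The article nowhere says that development cost is divided by 223. A unit cost based on expected reach could be worked out first and then applied to each man in the arm, and a fuller economic plan may do that. This stands as a limit on the point. It does not remove it, because the cost item and the ratio are both stated, the evaluation is called trial-based, and no audience is named.

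A second objection is that the modelled evaluation is the natural place for roll-out and that nothing prevents spreading the cost there. That is true, but as described it extends the time horizon and is silent on the number of viewers.

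Third, leaving development cost out altogether would omit a real cost, and including it is a transparent and conservative choice. This also stands, and is why both versions should be reported.

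Fourth, the economic evaluation is a secondary aim, which the Secondary objectives make conditional on a significant positive effect. The primary analysis is unaffected, and release depends on lack of net harm. This bears on the weight of the point.

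A reader might also infer that the planned bootstrap interval would be falsely narrow, since a constant per-man cost has no sampling variance. That does not follow for the ICER, because the constant is divided by a resampled effect. With SD 10, correlation 0.67 and 178 completers per arm, SE(E) = 10 × √0.5511 × √(2/178) = 0.79, so the 95% limits for E = 2.5 are about 0.96 to 4.04. A constant of AUD 1,345 per man then gives about AUD 333 to 1,404 per point, so the interval is not narrow. What resampling cannot show is the choice of divisor, which belongs in a sensitivity analysis.

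**Conclusion.** The point holds in a limited form. Followed as written, the plan gives an ICER whose development term is D/(n × E) and so depends on trial size and not on the intended audience. Against an assumed audience of 10,000 to 100,000, that term is about 45 to 448 times the per-viewer amount. This rests on two things: the plain reading that the average is taken over the trial arms, and the assumed audience sizes.

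Two stronger readings are not supported. A reader might infer that development is the largest cost or dominates the numerator. The article gives neither a production nor a service cost, and the services counted include inpatient admissions, so this cannot be known. A reader might also infer that the whole ICER shrinks in proportion as enrolment grows. Only the development term does, so the size of the effect on the full ratio is unknown.

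**What to change.** In the Cost-effectiveness analysis section:

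1. Report the within-trial ICER both with and without the one-off development cost, and state the divisor used in the version that includes it.
2. Report the development cost separately as a total.
3. In the modelled evaluation, divide that total by the expected number of viewers and add a sensitivity analysis over a stated range of audience sizes.

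This costs some rewording and one extra table, with no new data from participants. The small downside is that the audience size must be assumed and shown as a range.

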### Secondary objectives

To evaluate the effectiveness of the intervention on increasing help-seeking intentions and intentions to encourage other males to seek help from baseline (T1) to follow-up (T3) and to evaluate the effectiveness of the intervention on reducing scores on the masculine norm of self-reliance from T1 to T2 and T1 to T3, and male depression symptoms from T1 to T3. We also aim to evaluate the cost-effectiveness of the intervention if it is shown to have a significant positive effect on help-seeking intentions.

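### The bootstrap interval is placed on the ICER itself, and the ratio's denominator is not tied to the effect that must first be significant

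*Protocol article*

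**What the plan says.** The Cost-effectiveness analysis section of the protocol article defines the ICER as "the difference in average cost between the groups, divided by the difference in help-seeking intention scores". It places the uncertainty on that ratio: "Nonparametric bootstrapping will be used to obtain confidence intervals for incremental cost-effectiveness ratios". It names no cost-effectiveness plane, net benefit or acceptability curve. It does not say whether the score difference is the T2 or the T3 difference, nor that it is the contrast from the primary model. Mean costs and mean scores are to be assessed by generalised linear models.

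The Secondary objectives section sets a condition: "We also aim to evaluate the cost-effectiveness of the intervention if it is shown to have a significant positive effect on help-seeking intentions". The Cost-effectiveness analysis section does not repeat it.

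Three other places bear on the denominator:
- The primary outcome is the T1 to T2 change (Primary objective).
- The Health Service Use Questionnaire, which supplies service costs, is scheduled at T1 and T3 but not T2 (Table 1) and looks back four weeks (Secondary outcome measures).
- The authors expect the video alone to act quickly and briefly, and look to the wider campaign for a lasting effect (Primary outcomes, under Statistical analyses).

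**The concern.** A ratio can be ordered sensibly only while its denominator keeps one sign. A negative ICER can mean that the video costs less and works better, or that it costs more and works worse. As the effect difference crosses zero, the ratio jumps between very large positive and very large negative values. If a material share of replicates lies at or below zero effect, limits read from the ordered ratios pool opposite conclusions. A negative lower limit could then be read as possible cost saving when it comes mostly from replicates in which the video was dearer and worse.

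The condition in the Secondary objectives guards against this only if the estimate that must be significant is also the ICER's denominator. The document does not say that it is, and the timing of the cost data suggests it may not be.

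**Working it through.** **Inputs.** The Sample size section gives the design: "The sample size is calculated to detect a 0.25 standardised difference in mean on the GHSQ-Self score between the intervention and control group", with "90% power, 2-sided 5% significance level", "assuming a correlation of 0.67 between T1 and T2 scores" and "This sample size of 446 participants also allows for 20% loss to follow-up". Study design gives 223 per arm.

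**The plan's own figure.** With baseline adjustment, n per arm = 2(1.96 + 1.2816)²(1 − 0.67²)/0.25² = 185.3. Multiplied by 1.2 this is 222.4, so 223 per arm and 446 in total, as stated. How the 20% loss enters is a separate matter. Completers per arm: 223 × 0.8 ≈ 178.

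**Standard error of the effect difference, in SD units.**
- Baseline-adjusted: √[2(1 − 0.67²)/178] = 0.0787.
- Difference in change from the planned mixed model, with all T1 data used: √{2[(1 − 0.67²)/178 + (1 − 0.67)²/223]} = 0.0847.

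**Share of replicates at or below zero** (normal approximation) = Φ(−d/SE), where d is the observed effect.

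| Observed d | SE 0.0787 | SE 0.0847 |
|---|---|---|
| 0.25 | 0.07% | 0.16% |
| 0.20 | 0.6% | 0.9% |
| 0.15 | 2.8% | 3.8% |
| 0.10 | 10% | 12% |

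The share passes 2.5% when d falls below 1.96 × SE, that is 0.154 or 0.166 SD. This is also the two-sided 5% significance boundary.

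**Condition and denominator on the same contrast.** A significant positive effect requires d > 1.96 SE, so the share cannot exceed about 2.5%. With SE 0.0787 it averages 0.3% to 1.1% for true effects of 0.25 down to 0.05 SD.

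**Condition at T2, denominator at T3.** Assumptions: equal SE at both times (0.0787), correlation of the two estimates 0.5 to 0.8, and half or all of the T2 effect persisting. The entries are the percentage of trials meeting the T2 condition in which more than 2.5% of T3 replicates are at or below zero.

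| True T2 effect | Half persists | All persists |
|---|---|---|
| 0.10 SD | 67–78% | 33–52% |
| 0.15 SD | 69–74% | 21–35% |
| 0.20 SD | 66–69% | 12–19% |
| 0.25 SD | 60–61% | 5–8% |

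A hand check of the last row with half persisting: ignoring the condition, Φ(1.96 − 0.125/0.0787) = Φ(0.37) = 0.64. Selecting trials that were significant at T2 lowers this to about 0.60. With SE 0.0847 the overall ranges are 63–78% (half) and 7–55% (all). The mean share of non-positive replicates is 9% to 17% with half persisting, at SE 0.0787.

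**A second route, even at T2.** If the score difference is a raw T2 mean difference without baseline adjustment (an assumption), its SE is √(2/178) = 0.106. Among trials significant on the mixed-model contrast, 29% would then exceed 2.5% at a true 0.25 SD, and 55% at 0.15 SD.

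**What the mixing looks like.** The documents give no cost figures. Assume a cost difference of 50 with SE 30, independent of effect, and express the effect in units of its SE.
- Effect/SE = 1: point ICER 50, percentile interval −466 to 519. Dearer and worse: Φ(50/30) × 0.159 = 0.952 × 0.159 = 15.1% of replicates. Cheaper and better: 0.048 × 0.841 = 4.0%. Most negative ratios are therefore unfavourable ones.
- Effect/SE = 1.96 (just significant): point ICER 26, interval −27 to 176.
- Effect/SE = 3.24: point ICER 15, interval −3 to 51. Non-positive effects are 0.06% of replicates, so the interval reads normally.

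**The case against.** The strongest reply is that the evaluation is conditional. A reader of the Cost-effectiveness analysis section alone might infer that the method applies whatever the effect size, and calculate that more than 2.5% of replicates are non-positive in 16%, 57% and 78% of trials at true effects of 0.25, 0.15 and 0.10 SD (SE 0.0847). Those figures are simply the probabilities of not reaching a significant positive result. The Secondary objectives exclude such trials from the evaluation, so the figures do not describe the planned analysis. This part of the reply stands in full. It also disposes of the inference that trouble is likely for any effect below the design value: an observed 0.20 SD puts under 1% of replicates at or below zero.

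Other replies have some weight. The article does not state a percentile rule, so reading limits from ordered ratios is an inference. Mean costs and scores are reported by arm, so a careful reader can see the sign of each difference. Displays such as the plane or acceptability curve may be left to a fuller economic plan, and their absence alone would be no finding.

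What these replies do not answer is that the article commits to an interval on the ratio, while its condition protects that interval only if condition and denominator share a contrast. Group means, however clearly reported, do not give a mixed interval a meaning.

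**Conclusion.** The point holds in limited form. With the condition applied to the same T1 to T2 contrast that forms the denominator, the interval is mostly usable, though a just-significant result sits at the edge. The weakness is that the document leaves open a T3 or differently estimated denominator, which the condition does not protect. In the T3 case, about 60% to 78% of trials meeting the condition would have more than 2.5% non-positive replicates if half the effect persists, and about 5% to 55% if all of it does.

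These ranges rest on assumed persistence, an assumed correlation of 0.5 to 0.8, equal SEs at T2 and T3, and a normal approximation to the bootstrap. The document does not say that T3 will be used; the cost schedule only makes it plausible. Nor does it support calling the interval uninterpretable in general. Severity is minor: this is a conditional, secondary economic analysis, and the primary result is untouched.

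**What to change.** In the Cost-effectiveness analysis section:
1. Restate the condition from the Secondary objectives and say which contrast must be significant.
2. Name the time point and the estimator of the score difference used as denominator.
3. Keep the bootstrap, but show the joint cost and effect replicates on the cost-effectiveness plane. Add incremental net benefit and an acceptability curve over a stated range of values per GHSQ-Self point, so that no single willingness to pay has to be agreed.
4. Give an interval for the ICER only if essentially all replicates have a positive effect difference.

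This uses the same bootstrap output and no new data. It adds a few sentences and one or two figures. The downside is that readers may get a curve in place of a single interval.

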#### Plans to give access to the full protocol, participant-level data, and statistical code

The datasets analysed and statistical code used for analysis may be made available from the corresponding author on reasonable request.

## Oversight and monitoring

### Composition of the coordinating centre and trial steering committee

The Centre for Mental Health, Melbourne School of Population and Global Health, at the University of Melbourne, will be the trial coordinating centre. Staffing from the centre will consist of a trial manager (AN), who will be responsible for ensuring that the research team, study psychologists, and data management company (Strategic Data Ltd) conduct the trial, and that data is managed, in accordance with the protocol. There will be three additional internal researchers responsible for data collection (MF, SSR, JF). These researchers will meet weekly with the trial manager and will have other contacts as needed throughout the data collection phase. The two chief investigators (JP, SR) with have oversight of the project, with statistical and health economics advice and analyses provided by external experts (AM, LL, CM). In the months leading up to the trial, the chief investigators will meet weekly with the research team, including the trial manager and one external researcher with expertise in suicide prevention for men (ZS), to ensure all systems are in place to adhere to the protocol. Throughout the data collection phase of the trial (6 weeks), this group will meet on an as-needed basis, with daily contact between the internal chief investigator (JP) and the trial manager to ensure adherence to the protocol. This trial is one of seven RCTs that form part of a larger research programme (the Buoy Project). The chief investigators from these seven trials, and the trial manager from this trial, will meet monthly to receive trial updates and to discuss trial-related issues. This group of experienced researchers will act as the steering committee to this trial and can also provide ad hoc input to the trial as requested.

Given the relatively low-risk nature of the trial, a separate data monitoring committee will not be established.

### Adverse event reporting and harms

This is a low-risk intervention, and no significant adverse events or severe adverse events are anticipated. No adverse events were reported for the trial on which the methods are based [11], despite that trial testing a much longer (3-h) and suicide-specific video intervention. The most likely adverse event would be some increase in distress related to viewing the video, which has indirect references to suicide. We will provide the contact details of a study psychologist to all participants and encourage them to contact the psychologist should they experience any distress during and in the 4 weeks following participation in the trial. Any reported severe adverse events would be reported to the Human Research Ethics Committee that approved this protocol and advice sought from them regarding the actions required to respond to the specific event.

### Plans for communicating important protocol amendments to relevant parties

Any deviations from the protocol will be documented by the trial manager and signed off by the chief investigators. This document will then be stored by the trial manager with all other trial documentation. In addition, deviations from the protocol likely to have ethical implications will be reported to the Human Research Ethics Committee and advice will be sought on the necessary response to the deviation. The trial manager will also be responsible for updating the relevant entry in the Australian New Zealand Clinical Trials Registry (No. 12621001008819).

## Dissemination

We will prepare a lay summary of the outcomes of the RCT and will email it to all participants who indicate on the consent form that they are interested in receiving these results. We will publish several peer-reviewed journal articles and deliver presentations at national and international conferences. We will also deliver other presentations about the trial to other mental health and suicide prevention researchers and professionals. If the intervention video is shown to have no net negative effect on help-seeking, it will be publicly released and its release will be supported by a media campaign that will include the video on a project website with complementary content, social media dissemination, media interviews, and other strategies for increasing public interaction with the video.

